# Impact of a multifaceted early mobility intervention for critically ill children — the PICU Up! trial: study protocol for a multicenter stepped-wedge cluster randomized controlled trial

**DOI:** 10.1186/s13063-023-07206-2

**Published:** 2023-03-15

**Keywords:** Critical care, Intensive care unit, Pediatrics, Rehabilitation, Cluster randomized controlled trial

## Abstract

**Background:**

Over 50% of all critically ill children develop preventable intensive care unit-acquired morbidity. Early and progressive mobility is associated with improved outcomes in critically ill adults including shortened duration of mechanical ventilation and improved muscle strength. However, the clinical effectiveness of early and progressive mobility in the pediatric intensive care unit has never been rigorously studied. The objective of the study is to evaluate if the PICU Up! intervention, delivered in real-world conditions, decreases mechanical ventilation duration (primary outcome) and improves delirium and functional status compared to usual care in critically ill children. Additionally, the study aims to identify factors associated with reliable PICU Up! delivery.

**Methods:**

The PICU Up! trial is a stepped-wedge, cluster-randomized trial of a pragmatic, interprofessional, and multifaceted early mobility intervention (PICU Up!) conducted in 10 pediatric intensive care units (PICUs). The trial’s primary outcome is days alive free of mechanical ventilation (through day 21). Secondary outcomes include days alive and delirium- and coma-free (ADCF), days alive and coma-free (ACF), days alive, as well as functional status at the earlier of PICU discharge or day 21. Over a 2-year period, data will be collected on 1,440 PICU patients. The study includes an embedded process evaluation to identify factors associated with reliable PICU Up! delivery.

**Discussion:**

This study will examine whether a multifaceted strategy to optimize early mobility affects the duration of mechanical ventilation, delirium incidence, and functional outcomes in critically ill children. This study will provide new and important evidence on ways to optimize short and long-term outcomes for pediatric patients.

**Trial registration:**

ClinicalTrials.gov NCT04989790. Registered on August 4, 2021.

**Supplementary Information:**

The online version contains supplementary material available at 10.1186/s13063-023-07206-2.

## Background

### Background and rationale

Over 250,000 children are admitted to US pediatric intensive care units (PICUs) annually, leading to a 43% increase in the number of PICU beds since 2000 [1, 2]. While PICU mortality rates have decreased by over 50% in the last 2 decades, due to the changing spectrum of pediatric critical illness and medical advances, the decreased PICU mortality has led to a growing number of survivors experiencing both short and long-term morbidities [3–6]. Importantly, over half of all critically ill children develop preventable PICU-acquired morbidity, including iatrogenic opioid or sedative withdrawal, delirium, venous thromboembolism, pressure injury, and ICU-acquired muscle weakness, with the highest risk in mechanically ventilated patients [7–11]. These morbidities are strongly associated with poor functional recovery, which leads to decreased quality of life and increased parental stress [7, 12]. The resulting long-lasting physical, psychological, and neurocognitive impairments are known as pediatric post-intensive care syndrome (PICS-p) [3, 5, 6, 13]. The recognition of PICS-p has resulted in substantial research in adult ICU populations and is recognized by the NIH/NHLBI and major academic societies as a high research priority [14–17]. Thus, the preventable morbidities experienced by a growing number of PICU survivors are an important public health issue urgently in need of evidence-based strategies.

Early and progressive mobility is associated with improved outcomes in critically ill adults including shortened duration of mechanical ventilation and improved muscle strength [18–23]. However, the clinical effectiveness of early and progressive mobility in the PICU has never been rigorously studied. Unlike adults, critically ill children are admitted to the PICU during a crucial period of physical and neurocognitive development. Less than 40% of PICU survivors with normal baseline function recover to their baseline by 3 months after PICU discharge [7]. Moreover, our multicenter point prevalence study of physical rehabilitation in 82 US PICUs found that 68% of all admissions ≥ 3 days are patients ≤2 years old [24]. Thus, there is an urgent need to attend to both rehabilitation and habilitation, the acquisition of new physical and cognitive skills, in the PICU.

Despite the known harms of bed rest, a PICU culture of immobility is perpetuated by oversedation, physical restraints, and poor sleep hygiene due to a perceived need to optimize safety and comfort [25–27]. These factors all increase the risk of prolonged mechanical ventilation [28]. Single-component approaches to decrease the duration of mechanical ventilation in the PICU have not consistently shown effectiveness [29–32]. These issues have been mitigated in adult ICUs with early rehabilitation as part of the interprofessional ABCDEF bundle [33, 34]. The ABCDEF bundle is associated with lower mortality, less delirium, and more ventilator-free days in critically ill adults [33–35]. However, the heterogeneity of the PICU patient population limits the direct translation of this approach and has never been rigorously studied.

### Objectives

The objective of the study is to evaluate if the PICU Up! intervention, delivered in real-world conditions, decreases mechanical ventilation duration (primary outcome) and improves delirium and functional status compared to usual care in critically ill children. A secondary objective is to conduct a multi-stakeholder, mixed-methods process evaluation to identify key contextual factors associated with the delivery of PICU Up!.

### Trial design

This study is a mixed-methods, stepped-wedge, cluster randomized superiority trial of a pragmatic, interprofessional and multifaceted early mobility intervention (PICU Up!). The PICU Up! trial will include pediatric intensive care units (PICUs) from 10 discrete hospitals in the United States, with each PICU acting as one cluster. In this traditional stepped-wedge design, all clusters begin in the control group and then transition to the intervention group at sequential and randomly assigned periods, facilitating the delivery of the desired intervention to all clusters. Thus, randomization will occur at the level of the PICU unit. All participating PICUs will simultaneously start the baseline control period and data collection and plan their PICU Up! implementation process. The study includes an additional embedded process evaluation to identify factors associated with reliable PICU Up! adoption and performance. This study protocol is reported in accordance with the SPIRIT (Standard Protocol Items: Recommendations for Interventional Trials) guidelines [36, 37].

## Methods and analysis

### Study setting

The PICU Up! trial will include 10 PICUs in 10 states within the US representing a diverse mix of public, private, and federally funded teaching and nonteaching hospitals, of various sizes and patient populations; all included PICUs do not have an existing PICU mobility protocol and will not implement a mobility protocol until their randomized time of implementation. Participating sites were identified through informal surveys of pediatric critical care investigators and investigators participating in the Pediatric Acute Lung Injury and Sepsis Investigators (PALISI) Network. Historical PICU admission numbers were evaluated to ensure that the overall patient enrollment target is feasible.

### Eligibility criteria

All PICU patients, regardless of their length of stay, are screened for the PICU Up! unit-based intervention. Patients receiving invasive mechanical ventilation ≥ 48 h on day 3 of the PICU admission will be included in the study. Patients with active or anticipated withdrawal of life support within 48h, with an open chest or abdomen, or receiving extracorporeal membrane oxygenation (ECMO) will be excluded from the study (Fig. 1).

**Fig. 1 Fig1:**
[figure not shown]
Schedule of Enrolment, Interventions, and Assessments. * Intervention phase only. ^†^ On days when receiving invasive mechanical ventilation only

### Intervention

PICU Up! is a multifaceted, interprofessional, and systematic tiered pathway that is integrated into routine PICU practice to safely optimize early and progressive mobility. Detailed methodology for the development of the PICU Up! intervention has been published [38]. PICU Up! incorporates the screening process for determining a patient’s appropriate activity level into the daily rounding workflow for all PICU patients, with a tiered activity plan (Fig. 2) based on clinical parameters to individualize goals based on each child’s unique needs. Included are criteria for pausing activity and for reassessing the patient before continuing the activity [38]. While the PICU Up! level is based on objective criteria, the interprofessional team collectively determines the daily activity goal(s) through shared decision-making, which is documented in the medical record on morning rounds. The intervention includes a rounding template which ensures daily discussion of the PICU Up! level and elements: (1) analgesia; (2) protocolized extubation readiness testing; (3) sedation level and goal; (4) delirium screening; (5) mobility goal including PT/OT consultation by day 3; (6) family engagement in mobility; and (7) sleep promotion. As a pragmatic trial, all other aspects of PICU care will be conducted per routine practice.

**Fig. 2 Fig2:**
[figure not shown]
PICU Up! levels and corresponding activities

Prior to and during the baseline data collection phase, the clinical sites will develop a PICU Up! implementation strategy with guidance and resources from the Clinical Coordinating Center (CCC). The implementation planning will focus on local barriers and facilitators to early and progressive mobility for critically ill patients as well as goal-directed sedation, delirium prevention, extubation readiness assessments, sleep promotion, and family engagement. The PICU Up! Implementation Bundle includes discipline-specific educational resources (webinars, templates, educational presentations) and a unit-based electronic learning module to orient all PICU staff to PICU Up!.

As the intervention is administered by the clinical team to critically ill children, there no concerns related to patient adherence. Clinical team adherence to the core elements of the PICU Up! intervention will be monitored at both the patient and the unit level. Each site will receive periodic reports summarizing the PICU Up! compliance metrics. Individualized support will be provided by the CCC to sites to address adherence challenges.

### Timelines

After IRB approval and setup for data collection, all participating PICUs will simultaneously start the control period with data collection and continue implementation planning (Fig. 3). The order in which the PICUs will move into the intervention period will be determined through randomization. Each site will be notified of its transition date 4 months in advance. PICU Up! will be implemented over the following 3 months including PICU staff training. All PICUs will remain in the study for the entire study duration (i.e., 21 months), with each pair of PICUs being exposed to the intervention for different durations based on the randomization schedule.

**Fig. 3 Fig3:**
[figure not shown]
Stepped-wedge design for the PICU Up! trial

Identical, standardized data collection will occur during both the control and intervention phases. Figure 1 provides a timeline for enrolment, assessments, and interventions.

### Outcome measures

#### Primary outcomes

Our primary patient-level composite outcome is the number of days alive and ventilator-free (AVF) within the first 21 days after intubation or after PICU admission for patients intubated at an outside hospital. Days AVF within 21 days are defined as days when the patient was alive, and an endotracheal tube was absent for 24 continuous hours during a calendar day, ranging from 0 (any patient who experiences death prior to extubation or those intubated for more than 21 days) to 20 (patient is extubated the day following intubation and is alive by 21 days). If the patient was successfully extubated and discharged before 21 days, the days after discharge are ventilator-free. For patients discharged to a long-term ventilation rehabilitation facility, if such discharge happens before day 21, the patient will be considered to be mechanically ventilated for the remainder of the days to day 21. Days AVF was selected over the rank-based composite ventilator-free days given that expected mortality rates are relatively small and days AVF considers any day off the ventilator as important to the patient, family, and provider regardless of patient survival [4, 39–41].

#### Secondary outcomes

Secondary outcomes will include days alive and delirium- and coma-free (ADCF), days alive and coma-free (ACF), and days alive, as well as functional status at the earlier of PICU discharge or day 21, measured through Pediatric Cerebral Performance Category and Pediatric Overall Performance Category scores. If the patient was discharged from the PICU alive, all days following discharge will be considered days alive, delirium- and coma-free (Table 1).

**Table 1 Tab1:** Definition of outcome measures

**Primary outcome**	
Days alive and ventilator-free (AVF)	Days when the patient was alive, and an endotracheal tube was absent for 24 continuous hours during a calendar day^a,b^ through 21 days
**Secondary outcomes**	
Days alive and delirium- and coma-free (ADCF)	Days when the patient was alive, without delirium, and coma-free for 24 continuous hours during a calendar day^b,c,d^ through 21 days
Days alive and coma-free (ACF)	Days when the patient was alive, and coma-free for 24 continuous hours during a calendar day^b,d^ through 21 days
Days alive	Days when the patient was alive for 24 h during a calendar day^e^ through 21 days
Functional status	Pediatric Cerebral Performance Category and Pediatric Overall Performance Category scores assessed at the earlier of PICU discharge or day 21
**Exploratory outcomes**	
PICU length of stay	Number of days on which the patient was physically present in the PICU rounded to the nearest higher day through 21 days
PICU mortality	Number of patients deceased or withdrawn from the study for limitation of care orders or brain death evaluation/total enrolled patients
PICU and hospital discharge destination	Number of patients discharged to home, inpatient floor, inpatient, rehabilitation, other hospitals/number of discharged patients
New pressure injuries	Rate of new pressure injuries/eligible patient days through 21 days
Opioid exposure	Opioid dose (mg/kg/day) measured in morphine milligram equivalents (MME)^f^
Benzodiazepines exposure	Benzodiazepine dose (mg/kg/day) measured in midazolam milligram equivalents^g^

^a^ For patients with a tracheostomy, a ventilator-free day will be defined as a day when the patient is not receiving invasive mechanical ventilation for 24 continuous hours during a calendar day. Specifically, patients with a tracheostomy whose breaths are unassisted (i.e., trach collar) will be considered ventilator-free; patients receiving assisted breaths (i.e., CPAP) will not be considered ventilator-free

^b^ Days following PICU discharge to 21 days will be considered days alive, ventilator-, delirium- and coma-free, with the following exceptions: days after PICU discharge will not be considered days alive for deceased patients, days after PICU discharge will not be considered days ventilator-free if the patient remains intubated at discharge

^c^ Delirium-free days are days when the patient is at risk of delirium (i.e., coma-free) and delirium was not present

^d^ Coma-free days are days when all documented sedation scores are above the following thresholds: SBS ≥ − 1; RASS ≥﻿ −3; COMFORT-B ≥﻿ 10

^e^ For patients who were withdrawn from the study due to limitation of care orders or brain death evaluations, they will be considered deceased on the day death is pronounced

^f^ The following conversion will be used: fentanyl: 10 mcg = 1 MME; hydromorphone: 0.25 mg = 1 MME; morphine 1 mg = 1 MME [42]

^g^ The following conversion will be used: lorazepam: 0.5 mg = 1 midazolam milligram equivalents; midazolam: 1 mg = 1 midazolam milligram equivalents [43]

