### Sample size and power calculation

Site-specific admissions data previously published trial data, and data from the PICU Up! pilot multicenter trial were used to conservatively estimate that an average of 8 patients/cluster/month will be eligible for inclusion for data collection [24]. In the proposed stepped-wedge design, with two hospitals switching at each of the five steps, a total of 180 months of observation (90 months control/90 months intervention) will be available for analysis. Therefore, 720 patients are expected to be included in the baseline period and 720 in the intervention (post-implementation) period. The power calculation accounted for the clustered nature of the study design and the confounding effect of time using preliminary data obtained from our multicenter pilot trial [46]. Specifically, 1000 hypothetical stepped-wedge trials were simulated assuming patients within hospitals would be correlated with an intra-class correlation (ICC) of 0.01 and allowed the days AVF to day 21 to decline linearly over time (month 1’s mean (variance) of 13.2 (26.4) days AVF to day 21, with a monthly decline of 0.1 days) with a fixed effect of the intervention that is constant over time. Given the design, the anticipated sample size, type I error of 5%, and power of 80%, a ≥ 1.8-day improvement in mean days AVF to day 21 will be detectable between the intervention and control period, which is a clinically meaningful reduction in the duration of mechanical ventilation [29–31].

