### Data collection and management

Identical, standardized data collection will occur during both the control and intervention phases. Data collection includes patient demographic, clinical, and rehabilitation data from the Epic electronic health record (EHR) from PICU admission through the earlier of day 21 or PICU discharge. The Data Coordinating Center (DCC) and CCC will provide oversight for all relevant study-related activities. The composition of the DCC and CCC are specified in Additional file 1. Data will be captured, managed, and exported using a secure, auditable, and HIPAA-compliant database (REDCap) with unique de-identified research participant identifiers [47]. The REDCap database will include automated data validation, range checks, branching logic, and designating fields as required. Data quality will be ensured through protocolized data collection, staff training and re-training on protocols, and auditing, independent of investigators and the sponsor. Auditing by the DCC includes initial and ongoing quality assurance procedures, periodic data cleaning, regular data queries, and PICU Up! performance feedback to sites [48].

The clinical trial will collect data on potential adverse events prospectively; this data will be reviewed daily, and reports will be made to the Data Safety Monitoring Board (DSMB), Institutional Review Board (IRB), and sponsor as required.

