The primary analysis for all outcomes will be unadjusted, that is, we will assume that patients enrolled in the study over time will be similar with respect to characteristics associated with the outcomes (e.g., age and severity of illness). Secondary analyses will include exploratory analyses to evaluate this assumption and the models (described above) will be extended to include an adjustment for key patient characteristics (e.g., age, admission diagnosis category, measures of baseline function such as PCPC, POPC, FSS). Analyses to detect significant differences in the intervention effect among sex/gender will be conducted. Additional secondary analyses will fit the models described above, including adjustment for the patient-specific measure of PICU Up! performance by separately including the measure of proportional performance (ranging from 0 to 1) and the binary indicator of a complete performance.

Statistical significance will be set at *p*-value < 0.05 using a two-sided hypothesis test for the primary outcome analysis; all secondary analyses will be considered exploratory with two-sided 95% confidence intervals reported. We will conduct missing data assessment/estimation, and if necessary, employ methods for imputation of missing data using the MICE package [50].

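### Discharge destination is calculated among discharged children only and PICU length of stay has no rule for death, so both exploratory outcomes can look better when mortality rises

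*Protocol article*

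**What the plan says.** All the definitions at issue are in Table 1 of the protocol article, under Outcome measures.

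- **PICU length of stay** is defined as "Number of days on which the patient was physically present in the PICU rounded to the nearest higher day through 21 days". The row carries no footnote. Footnotes a to e belong to the day-count outcomes (primary and secondary), and f and g to the drug exposures.
- **PICU and hospital discharge destination:** "Number of patients discharged to home, inpatient floor, inpatient, rehabilitation, other hospitals/number of discharged patients". None of the categories is death or still in the PICU.
- **PICU mortality**, between these two rows, uses a different denominator: "Number of patients deceased or withdrawn from the study for limitation of care orders or brain death evaluation/total enrolled patients".
- **Footnote b**, attached to the ventilator-, delirium- and coma-free day counts, deals with death explicitly: "days after PICU discharge will not be considered days alive for deceased patients".

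Data collection and management sets the data window: "from PICU admission through the earlier of day 21 or PICU discharge". The Primary outcomes section gives no mortality rate and says only that "expected mortality rates are relatively small". Under Patient-level outcomes, "all secondary analyses will be considered exploratory with two-sided 95% confidence intervals reported". The statistical methods give no competing-event, composite or survivor-only rule for length of stay or destination.

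**The concern.** The two rows handle death differently from the rest of the table. The day-count outcomes give no credit for days after death, and mortality is taken over everyone enrolled. Length of stay simply stops counting when a child dies, so a death on day 6 and a discharge on day 6 both score 6, and both look better than a survivor who leaves on day 12. Destination is computed in a subgroup formed after treatment. If the intervention changes who survives, the discharged children in the two periods are no longer comparable groups.

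Confidence intervals are promised for exploratory analyses, and readers will take an interval on stay or destination as an effect on patients. A shorter stay or a better destination mix could then partly reflect more deaths, and a worse mix could partly reflect fewer.

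**Working it through.** The plan states no figure for either outcome, so there is none to reproduce. The check is of direction and rough size. The group size comes from the Sample size section: "720 patients are expected to be included in the baseline period and 720 in the intervention (post-implementation) period". Mortality, lengths of stay and destination counts are **assumptions**, because the protocol gives none.

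**Length of stay**

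Let m be mortality, S the mean stay of survivors and D the mean stay of children who die.

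Mean stay = m × D + (1 − m) × S

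If only mortality changes, by Δm, the mean changes by −Δm × (S − D). With S assumed at 11 to 14 days and D at 5 to 8 days, S − D runs from 11 − 8 = 3 to 14 − 5 = 9 days.

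| Rise in mortality | Apparent fall in mean stay (days) |
|---|---|
| 2 points | 0.02 × 3 = 0.06 to 0.02 × 9 = 0.18 |
| 3 points (5% to 8%) | 0.03 × 3 = 0.09 to 0.03 × 9 = 0.27 |
| 5 points (5% to 10%) | 0.05 × 3 = 0.15 to 0.05 × 9 = 0.45 |

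Survivors' stay is unchanged throughout, so the whole fall is produced by deaths.

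**Discharge destination**

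Take 720 children per period. In this first set, children still in the PICU at day 21 are assumed to have no recorded destination.

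| Scenario | Died | Still in PICU | Home/floor | Rehabilitation/other | Home/floor among discharged | Home/floor among all enrolled |
|---|---|---|---|---|---|---|
| Control | 36 | 144 | 432 | 108 | 432/540 = 80.0% | 432/720 = 60.0% |
| A: 36 extra deaths, all among children bound for rehabilitation/other | 72 | 144 | 432 | 72 | 432/504 = 85.7% | 60.0% |
| B: 36 extra deaths, spread in proportion | 72 | 144 | 403 | 101 | 403/504 = 80.0% | 403/720 = 56.0% |
| C: 36 more children leave the PICU by day 21, to rehabilitation/other | 36 | 108 | 432 | 144 | 432/576 = 75.0% | 60.0% |

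In A, harm looks like benefit. In B, harm is hidden rather than reversed. In C, more children leaving the PICU looks like a worse result, with no change in mortality.

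Scenario C needs the data window to govern this outcome, but the effect of deaths does not. Suppose instead that the 144 children are followed to discharge and split 80:20 like the others. The control period then has 432 + 115.2 = 547.2 home/floor among 720 − 36 = 684 discharged, again 80.0%. With 36 extra deaths as in A, the share is 547.2/648 = 84.4%, while the share of all enrolled stays at 547.2/720 = 76.0%.

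**The case against.** The case for leaving the definitions alone has real weight.

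- **Days physically present are a legitimate measure of bed use.** A bed-day not used after a death is a real resource quantity, and the protocol does not claim that a shorter stay means a better outcome for the child. This stands, and it is a reason to keep raw days as a descriptive measure.
- **The reader is not left blind.** PICU mortality and days alive are reported alongside, and a mortality shift large enough to matter should show there. Expected mortality is described as small, and excluding children with anticipated withdrawal of life support removes some early deaths. This limits the importance of the point but does not repair the two definitions.
- **An analysis plan could add a rule for death.** It could for length of stay. The discharged-only denominator, however, is written into Table 1 and is not a detail left open.
- **The destination row has no day-21 limit.** Unlike the length-of-stay row, it carries no such restriction, and hospital destination necessarily falls after PICU discharge for a child sent to the floor. That children still in the PICU drop out is therefore conditional: it holds only if the stated data window governs this outcome.

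Two stronger readings are tempting and are not supported. A reader might infer that faster discharge could lengthen measured stay by bringing sicker children into the count. It cannot: faster discharge reduces days present, and the row has no survivor or discharge restriction. Selection after treatment affects destination only. A reader might also score a death on day 6 as 21 days and take 0.02 × (21 − 6) = 0.3 day as the bias from a 2-point mortality difference. That is the gap between two scoring rules. The distortion of the mean as defined is the 0.06 to 0.18 day shown in the working.

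**Conclusion.** The point holds as a minor one. Followed exactly, Table 1 gives a destination comparison conditioned on an event after treatment and a stay measure that credits early death. Both can look better when mortality rises. This is a possibility shown by example, not a demonstrated bias.

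The direction for stay assumes that children who die have shorter stays than survivors. The direction for destination assumes that the extra deaths fall mainly among children bound for less favourable destinations. For stay the distortion is a fraction of a day at any plausible change in mortality. For destination it was 4 to 6 percentage points in the examples, with counts that are wholly assumed. The loss of children still in the PICU at day 21 is a second, conditional route. The primary outcome, the sample size and control of the type I error are not touched.

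**What to change.** In Table 1 and the derivation code:

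1. **Destination.** Divide by all enrolled children and add died and still in PICU at day 21 as categories. State how children withdrawn for limitation of care or brain death evaluation are classed, so that the row agrees with the mortality row. The sponsor should confirm that hospital destination is collected beyond the stated data window. If it is not, the row should be limited to PICU destination.
2. **Length of stay.** Use days alive and out of the PICU through day 21 as the comparative measure. Counting the discharge day as a PICU day and ignoring readmission, a child discharged on day 6 scores 21 − 6 = 15, one discharged on day 12 scores 21 − 12 = 9, and a child who dies in the PICU on day 6 scores 0. Keep raw PICU days as a descriptive utilization measure.

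The cost is a wording change and slightly more derivation work. For the PICU-level items the inputs are already within the data collected; hospital destination is the one to confirm. The downside is a less familiar measure than raw stay, which remains available alongside it.

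### A child who leaves the PICU still delirious or comatose is scored free of both from the next day, so for these children ADCF and ACF depend on when they are discharged

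*Protocol article*

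**What the plan says.** ADCF and ACF are secondary outcomes counted through day 21. While the child is observed the standard is strict. An ADCF day is defined by "Days when the patient was alive, without delirium, and coma-free for 24 continuous hours during a calendar day" and an ACF day by "Days when the patient was alive, and coma-free for 24 continuous hours during a calendar day". Footnote c adds: "Delirium-free days are days when the patient is at risk of delirium (i.e., coma-free) and delirium was not present".

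After PICU discharge a default replaces observation. Footnote b of Table 1, which both outcomes cite, reads: "Days following PICU discharge to 21 days will be considered days alive, ventilator-, delirium- and coma-free, with the following exceptions". It then makes two exceptions. One is death, which removes the day as a day alive and so also from ADCF and ACF. The other touches ventilation only: "days after PICU discharge will not be considered days ventilator-free if the patient remains intubated at discharge".

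The Secondary outcomes text repeats the credit: "If the patient was discharged from the PICU alive, all days following discharge will be considered days alive, delirium- and coma-free". The section on data collection and management says that data run "from PICU admission through the earlier of day 21 or PICU discharge".

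**The concern.** The protocol accepts that leaving the PICU does not end ventilation. Footnote b carries intubation forward, and the Primary outcomes section treats a child sent to a long-term ventilation facility as ventilated to day 21. Nothing comparable exists for delirium or coma, and no reason is given. A child discharged still intubated loses ventilator-free days but is credited with delirium- and coma-free days to day 21. Because data collection stops at discharge, the assigned brain state is never checked.

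At stake is what the trial may say about delirium, which the Objectives section names as something PICU Up! is meant to improve. The secondary outcomes are analysed as mean differences from linear mixed models, so credited days enter the estimate directly. The intervention could plausibly change discharge timing: PICU length of stay is an exploratory outcome, and the Blinding section states that the trial is unblinded. Part of any ADCF or ACF difference could then reflect when observation stopped and not how long delirium or coma lasted.

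**Working it through.** The article gives no planning figure for ADCF or ACF, so there is none to reproduce. The check is a day count under the stated rule.

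**Inputs.** The horizon is 21 days (Table 1). The child survives to day 21, so the death exception does not apply. Delirium or coma is present on every day 1 to B, and PICU discharge is on day D. B and D are illustrative.

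**Formulas.**

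- Footnote b: score = 21 − min(D, B)
- True course: score = 21 − B
- Excess credit: B − min(D, B), which is zero when D ≥ B and B − D when D < B

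**Results for single children.**

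| Last affected day B | Discharge day D | Footnote b | True course |
|---|---|---|---|
| 14 | 14 | 21 − 14 = 7 | 7 |
| 14 | 12 | 21 − 12 = 9 | 7 |
| 14 | 10 | 21 − 10 = 11 | 7 |
| 14 | 8 | 21 − 8 = 13 | 7 |
| 10 | 14 | 21 − 10 = 11 | 11 |
| 10 | 8 | 21 − 8 = 13 | 11 |
| 8 | 8, 10, 12 or 14 | 21 − 8 = 13 | 13 |
| 21 (comatose throughout, ACF) | 8 | 21 − 8 = 13 | 0 |

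Three things follow. With B = 14, each day of earlier discharge adds a full day. With B = 10, moving discharge from day 14 to day 8 adds only 13 − 11 = 2 days, because the child was clear after day 10 anyway. With B = 8, the discharge day changes nothing.

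**Mean shift.** If a share q of children remain affected until the later of two discharge days, and they leave g days earlier, the mean rises by q × g with the clinical course unchanged. The documents give neither q nor g. Over the assumed range q = 0.05 to 0.30 and g = 1 to 4 days:

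- lowest: 0.05 × 1 = 0.05 days
- highest: 0.30 × 4 = 1.2 days

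**Full carry-forward as the alternative.** Suppose a child affected on the last assessed PICU day gets no credit after discharge. For B = 12 and D = 8:

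- true score: 21 − 12 = 9
- footnote b: 21 − 8 = 13, error +4
- carry-forward: 0, error −9

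With 10% to 30% of children affected (assumption) and discharge on days 8 to 12, each affected child loses 21 − 12 = 9 to 21 − 8 = 13 credited days. Mean ADCF then falls by 0.10 × 9 = 0.9 to 0.30 × 13 = 3.9 days. Carry-forward also depends on discharge timing, in the opposite direction: with B = 12, discharge on day 14 scores 9 and discharge on day 8 scores 0.

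If children clear at discharge stay clear, each child's true score lies between the two rules.

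**The case against.** The best defence is that the rule is explicit, the same in the text and in the footnote, and applied identically in both phases. The primary outcome does not use it for brain state. The Statistical methods section calls all secondary analyses exploratory and reports confidence intervals only. PICU length of stay is reported, so readers can see whether discharge timing moved. Intubation at discharge is a known treatment state, whereas a last positive delirium screen is a point assessment, so carrying it forward for up to 13 days does not follow from the ventilator rule. Sensitivity analyses are often left to an analysis plan, which is not shown here.

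Much of this stands. It limits the weight of the point, and the over-correction shown above is a sound reason not to make carry-forward the main definition. Two parts do not answer the point. The article states the rule twice and lists its exceptions, so this is a rule as fixed and not a detail deferred. And length of stay over all children does not show whether timing changed among those who left delirious or comatose, nor how many they were.

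A reader might infer that earlier discharge by itself raises ADCF and ACF. The documents do not support that: it does so only for children still affected at the earlier discharge day. A reader might also put a size on the bias by taking 1.8 days as the reduction in stay, giving 0.10 × 1.8 = 0.18 to 0.30 × 1.8 = 0.54 days. But 1.8 days is the detectable difference in ventilator-free days in the sample size section. Nothing equates it with a change in PICU stay.

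**Conclusion.** The point holds in limited form. For a child who leaves the PICU delirious or comatose, the stated rule makes ADCF (and ACF, if comatose) depend on the discharge day, by up to one day per day of earlier discharge. Nothing collected later can correct it.

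This becomes a bias between phases only if PICU Up! changes discharge timing among such children. That is plausible but not documented. The 0.05 to 1.2 day range rests on assumed shares and assumed changes in stay, and on brain state outlasting the discharge day. It shows sensitivity and does not predict the bias. Coma at discharge is probably rarer than delirium, so ADCF is likely the more exposed outcome, but the article gives no rates.

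The primary outcome and its test are unaffected. What is limited is any statement that the intervention improved delirium or coma.

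**What to change.** Keep footnote b as the main definition and prespecify one bounding sensitivity analysis. Children with delirium (for ADCF) or coma (for ADCF and ACF) on the last assessed PICU day receive no free days after discharge. Report the number of such children by phase. Claim an improvement in delirium or coma only if the two analyses agree in direction.

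The cost is a few sentences and a recoding of data already collected.

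The drawbacks should be stated with it. The bound under-credits children whose delirium clears soon after discharge and can penalise earlier discharge, which is why it should be a bound and not the main rule. It brackets each child's score, and so each phase mean. Applying the same rule to both phases does not strictly bracket the difference between them, so agreement in direction is a check and not proof. Delirium screening is itself an element of PICU Up!, so the counts should also show how many children in each phase had no assessment on their final PICU day. If few children are affected in either phase, the counts alone will show that the convention is harmless.
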